### Allocation concealment

On the day of the usual medical consult, inclusion and exclusion criteria will be verified and a written informed consent obtained by the physician. Once the patient is included in the trial, the information will be given to the GHdC pharmacy to enter the patient on the randomization list. The pharmacist of the GHdC will create the randomization list using a computer-generated allocation sequence and will be the only source of access to the randomization key. Patients will be randomized in a 2:1 ratio (S-ketamine: control) in blocs of 15 (S-ketamine 10: control 5). The same randomization method will be used for the two studied cohorts.

Only the person responsible for the randomization, independent from the study protocol, will have the randomization key. The randomization list and a copy will be edited, placed in a sealed envelope, and kept at the GHdC pharmacy.

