#### S-ketamine: investigational medication drug

Because this study is a dose-escalation type of study, we have chosen two dose regimens: low-dose S-ketamine at 0.2 mg/kg and high-dose S-ketamine at 0.4 mg/kg, both in kilograms of corrected ideal body weight according to the Lorentz formula [20]. These doses are subanesthetic and suitable and secure for ambulatory administration [21, 22]. They are consistent with equianalgesic ketamine doses recommended for pain treatment, as well as our current clinical practice [11, 14, 23].

S-ketamine will be prepared by the GHdC pharmacy, which will condition ampoules of S-ketamine (25 mg/ml) under a laminar flow hood into syringes of 2 ml containing 25 mg/ml of S-ketamine. Each syringe will have identical packaging with a recognition number linked to the randomization. These syringes will be sent to the pain clinic, where the responsible physician will prepare the right dosage of S-ketamine according to the patient’s weight and dilute it in physiological saline (0.9% NaCl) to obtain a volume of 45 ml. The product will be administered intravenously over 3 h (15 ml/h) with an electronic syringe pump.

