**Assessments:**								
***Central Sensitization Inventory (CSI)***			X					X
***EQ5D-5 L***			X					X
***Hospital Anxiety and Depression Scale (HADS)***			X					X
***Brief Pain Inventory (BPI)***			X	X	X	X	X	X
***Patient Global Impression of Change (PGIC)***			X	X	X	X	X	X
***Adverse events***			X	X	X	X	X	X

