#### Primary outcome

Our primary outcome is improvement in pain and/or functional status. Improvement will be defined as clinically significant as follows: for pain relief, a 2-point decrease in the Brief Pain Inventory (BPI) pain severity score [29], and for functionality, a one-point decrease on the BPI pain interference scale [28]. We will compare the proportions of patients with clinically significant improvement in each of these metrics between the S-ketamine and placebo groups.

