#### Secondary outcomes

Our secondary outcomes are a 50% pain decrease on a numerical rating scale, impact on quality of life as evaluated using the EQ5D-5 L questionnaire, impact on emotional status using the Hospital Anxiety and Depression Scale questionnaire, and the incidence of adverse events solicited and spontaneously reported to the pain clinic staff. We also will assess patient global satisfaction with the treatment, as evaluated using the Patient Global Impression of Change questionnaire.

All questionnaires will be completed before drug administration, and during the follow-up visits together with secondary outcomes assessments (Table 1).

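### Allocation comes before the first BPI, so a patient lost before T0 is randomised with no baseline and no outcome

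*Protocol article*

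**What the plan says.** **Order of events.** Under Allocation concealment, eligibility and consent come first: "On the day of the usual medical consult, inclusion and exclusion criteria will be verified and a written informed consent obtained by the physician". Allocation follows: "Once the patient is included in the trial, the information will be given to the GHdC pharmacy", which then adds the patient to its randomisation list. Table 1 (Regimen) puts enrolment at two weeks before T0. Allocation has its own column, running from that point to T0 and standing before the T0 column.

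**First BPI.** In the Table 1 row for "Brief Pain Inventory (BPI") there are six marks: T0 and weeks 2, 4, 6, 9 and 12. There is none at enrolment or in the allocation column. The first marks for EQ5D-5L and HADS are also at T0. Secondary outcomes agrees with this timing: "All questionnaires will be completed before drug administration, and during the follow-up visits together with secondary outcomes assessments (Table 1").

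**Primary endpoints.** The pain endpoint is "a 2-point decrease in the Brief Pain Inventory (BPI) pain severity score" and the function endpoint is "a one-point decrease on the BPI pain interference scale".

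**Analysis set.** The Abstract commits to intention to treat. Missing data takes out of the study anyone who misses one of the three treatment or three follow-up appointments and counts that person as lost. Missing data and Statistical analysis also plan multiple imputation, for outcomes and for covariates.

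**The concern.** A responder defined by a decrease cannot be classified without the score from which the decrease is counted. Here that score is first recorded after the patient has been allocated. Anyone who withdraws or fails to attend between allocation and T0 is a randomised patient with no baseline, no infusion and no later BPI.

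The plan points in different directions for such a patient. Intention to treat keeps the patient in. The missed-appointment rule takes the patient out, because T0 is one of the three treatment appointments. Multiple imputation would have to supply every BPI value with no observed BPI from that patient to build on. At stake are some evaluable patients in each cohort and a clear statement of who is in the primary analysis. The timing of allocation creates this group, so a change of timing can largely remove it.

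**Working it through.** No sample size or power figure carries this point. The check sets the schedule against the endpoint definition and then sizes the loss under stated assumptions.

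**1. Schedule (Table 1, with Allocation concealment)**

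| Step | Enrolment, T-2 weeks | Allocation window, up to T0 | T0 |
|---|---|---|---|
| Eligibility and consent | X | | |
| Allocation | | X | |
| First BPI, EQ5D-5L, HADS | | | X |
| First infusion | | | X |

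Allocation is in the second time column and the first BPI in the third. A loss between the two leaves an allocation and no BPI.

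**2. Endpoint.** Responder status is (T0 score minus follow-up score) at or above the threshold: 2 points for severity, 1 point for interference. For a patient lost before T0 both terms are missing, so neither endpoint can be computed.

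**3. Which rule applies.** The missed-appointment rule gives exclusion. The intention-to-treat statement gives inclusion. Inclusion through multiple imputation means imputing the T0 score and all five later scores.

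**4. Drop-out allowance (Sample size estimation).** The plan inflates 55 to 70 per group for 20% drop-out. Check: 55 / (1 − 0.20) = 68.75, or 69 rounded up, so 70 is consistent; 70 × 0.80 = 56 remain. No separate figure is given for loss before T0.

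**5. Size.** The Abstract gives 105 patients per cohort at 2:1, which is 70 on S-ketamine and 35 on control. The documents give no rate of loss between allocation and T0, so the rates below are assumptions.

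| Assumed loss before T0 | Of 105 | Of 70 S-ketamine | Of 35 control |
|---|---|---|---|
| 2% | 2.1 | 1.4 | 0.7 |
| 5% | 5.25 | 3.5 | 1.75 |
| 10% | 10.5 | 7.0 | 3.5 |

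That is about 2 to 10 patients per cohort. If allocation follows the T0 questionnaires, loss before T0 happens before randomisation and this group disappears.

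**The case against.** The strongest reply is that little harm follows.

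- **Bias.** A reader might infer that a baseline taken after allocation is compromised, or is weaker as a covariate. The documents do not support this. The pharmacy alone holds the key (Allocation concealment), the trial is double-blind, and questionnaires are completed before the drug is given. A T0 score cannot respond to an allocation that nobody in the clinic knows, and loss before T0 should not differ by arm. This objection stands in full.
- **Dilution.** A reader might infer that untreated patients dilute the comparison. That would need them to be counted as non-responders or as untreated. The plan excludes or imputes instead, so dilution does not follow.
- **Drop-out allowance.** Nothing limits the 20% to losses after dosing. Early losses may fall within it, as intended. This stands, although such losses remain avoidable.
- **Length of the gap.** The window ends at T0 and no day is fixed, so the gap may be short. This limits the size of the problem but does not remove it.
- **Completeness of Table 1.** A CSI above 40 is an inclusion criterion, yet the first CSI mark is at T0, so the table may not list every administration. An unlisted earlier BPI is possible, but no text mentions one, and Secondary outcomes refers to the same table for timing.
- **Eligibility and pregnancy.** A reader might also conclude that eligibility or pregnancy status is never checked again before treatment. That would rest only on silence in a condensed article and is not claimed here.
- **A wider conflict.** Exclusion after a missed visit conflicts with intention to treat at the later visits too, and moving allocation does not settle that. This is correct. The present point concerns only the group lost before T0, which the schedule itself creates.

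**Conclusion.** The point holds in a limited form. As written, patients are allocated after inclusion and before the only baseline BPI that the article schedules. A patient lost in between has no BPI at all and no settled place in the analysis: the missed-appointment rule and the intention-to-treat statement disagree.

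The expected cost is avoidable loss of information and an unclear intention-to-treat set. No bias is shown. The size is about 2 to 10 of 105 per cohort, and it rests entirely on an assumed loss of 2% to 10% before T0; the true figure could be smaller if allocation usually happens close to T0. The timing follows from the text and Table 1. The change is worth making because it looks inexpensive, not because the present schedule would invalidate the result.

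**What to change.** In Table 1 and Allocation concealment, move allocation to the T0 visit, after the baseline BPI, EQ5D-5L and HADS are completed and before the first infusion. The pharmacy would release the next numbered syringe that day.

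The preparation sections suggest that this can work. The 2 ml syringes are uniform ("Each syringe will have identical packaging with a recognition number linked to the randomization"), the placebo syringes match them, and the weight-based amount is drawn up in the clinic. The article gives neither shelf life nor same-day release capacity, so the pharmacy must confirm feasibility.

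The cost is a wording change in two places and the need to have syringes ready on the day of T0.

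If same-day release is not possible, collect a BPI before allocation, keep allocation as close to T0 as the pharmacy allows, and state which BPI is the baseline. This is a partial remedy: a patient lost before T0 would then have a baseline but still no outcome. In that case the plan should also say how such a patient is analysed, so that the Abstract and the Missing data section agree.

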### Sample size estimation

The sample size was calculated based on a cross-sectional sample of 25 patients already treated with ketamine (dose equivalent to 0.2 mg of S-ketamine), magnesium sulfate, and clonidine for whom we compared data before and 2 weeks after treatment. Applying our primary outcomes, we found that 28% (*n* = 7) met the pain relief objective and 56% (*n* = 14) met the functionality objective. Few data were found concerning a placebo effect, which we assessed at 10% under the conditions of our trial (data extrapolated from Noppers et al. [22]).

The selected size of the study population was calculated based on 0.8 (80%) power at an alpha of 0.0125. The alpha is set to 0.0125 because we will compare two primary outcomes twice, at most: the first comparison will be between the usual care+placebo treatment and usual care+low-dose S-ketamine treatment. If this comparison shows non-significant difference between the two groups, the second comparison will be between the usual care+placebo treatment and the usual care+high-dose S-ketamine treatment. Thus, for the primary outcome, a total of four comparisons will be made, so we divided the targeted *p* value (0.05) by this number of comparisons to arrive at a *p* value that allows for rejection of the null hypothesis of no difference observed between the groups. With a minimum clinically relevant difference of 5%, an expected rate of 10% improvement for the usual care+placebo group, and an expected rate of 25% improvement for the usual care+S-ketamine group, 55 patients per group are needed. Considering a drop-out rate of 20%, 70 patients per group will be needed to ensure that data for 55 per group will be available at the end of follow-up.

This number of patients for inclusion is ambitious, but the pain center treats more than 100 patients with fibromyalgia per year. The duration of recruitment is expected to be one year for the first dose cohort and one more year if a second cohort of patients is needed.

All patients will be recruited by the physicians of the pain clinic during their medical consult, according to the described eligibility criteria (Fig. 3).

**Fig. 3 Fig3:**
[figure not shown]
Recruitment process. CSI, Central Sensitization Inventory; EULAR, European League Against Rheumatism

As noted, MI will be applied, using the mitml R package. Indeed, maximum likelihood and MI, using all available data in the study, will produce unbiased estimates of the treatment effect and correct *p* values. MI also is a method of choice because it allows for imputation of missing values on the outcome and on the covariate [35] and is valid for the three missingness categories (missing completely at random, missing at random, and missing not at random) [36]. Models obtained via maximum likelihood and MI will be compared. For continuous outcomes, we will look at the residuals of the model, and if these are not normally distributed, we will use the bestNormalize R package to transform the outcome and report the results of this last linear mixed model.

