### Missing data

Participants who do not present for one of the three treatment appointments or one of the three follow-up appointments will be excluded from the study and considered as lost to follow-up. To minimize missing data, pain clinic staff will supervise questionnaires’ completion, ensuring they are adequately filled.

In cases of missing data, we will analyze the cause, according to Rubin [30], and will test whether the data are missing completely at random, missing at random, or missing not at random. Multiple imputation (MI) for longitudinal data will be applied.

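### Multiple imputation is said to be valid even when data are missing not at random, and a test of the mechanism is promised; neither holds as specified

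*Protocol article*

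**What the plan says.** All references are to the protocol article.

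The Statistical analysis section gives, as a reason for choosing MI, that it "is valid for the three missingness categories (missing completely at random, missing at random, and missing not at random". It says that ML and MI, by using all available data, "will produce unbiased estimates of the treatment effect" and correct p values. No condition on the reason for missingness is attached. It then says: "Models obtained via maximum likelihood and MI will be compared". No purpose is given for that comparison.

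The Missing data section says: "In cases of missing data, we will analyze the cause". In the same sentence the team "will test whether the data are missing completely at random, missing at random, or missing not at random". It continues: "Multiple imputation (MI) for longitudinal data will be applied". The only other detail is the R package (mitml). The article names no imputation model that departs from MAR. The same section says that a participant who misses one of the six appointments "will be excluded from the study and considered as lost to follow-up".

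Two other statements bear on the point. The Sample size estimation section plans for 20% drop-out. The Abstract and the Statistical analysis section make the first cohort's result decide whether the trial ends or goes on to the second dose.

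**The concern.** Under MAR, the chance that a score is missing does not depend on the unseen score once the modelled data are taken into account. Likelihood-based mixed models, and imputation from a model fitted to the observed data, rely on this. Under MNAR they are in general biased. MI can be made valid under MNAR, but only if the imputation model states how unseen scores differ from what MAR predicts, and nothing of that kind is specified.

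The promised test has a related problem. Evidence against MCAR can be found by relating missingness to observed data. No test on observed data alone can tell MAR from MNAR, because the two differ only in the values nobody saw.

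Informative drop-out is plausible here. The Patient monitoring section lists non-attendance for treatment and serious adverse events among the reasons for discontinuation, and the Blinding section acknowledges dysphoric effects of ketamine. Someone who relies on the stated validity could report a biased responder difference as unbiased, and that difference could end the trial at the first cohort.

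**Working it through.** **1. The plan's own figure.** From the Sample size estimation section: 55 evaluable per group and 20% drop-out. 55 / (1 − 0.20) = 68.75, so 69, against 70 stated. The 20% allowance reproduces to within rounding. The 55 is taken as given here.

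**2. Why MAR and MNAR cannot be separated.** 105 patients at 2:1 give 70 on S-ketamine and 35 on control. With 20% missing on S-ketamine, 14 are unseen and 56 are seen. At the planned 25%, 14 of the 56 respond. If none of the unseen patients respond, the true rate is 14/70 = 20%. If all do, it is 28/70 = 40%. Every value between fits the observed data equally well, so no test can choose among them. The same argument applies within any level of the earlier scores.

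**3. Size of the possible error.** For each arm, true rate = observed rate × (1 − d) + d × (rate among drop-outs), where d is the proportion missing. The observed rates are the plan's 25% and 10%. Assumed: drop-out behaviour as shown, and earlier visits tell the imputation nothing, so MAR imputation returns 25 − 10 = 15 points in every row.

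| Assumed drop-out | S-ketamine | Control | True difference | Overstated by |
|---|---|---|---|---|
| 20% in both arms, all non-responders | 0.8×25 = 20% | 0.8×10 = 8% | 12 | 3 |
| 20% in both arms, drop-outs respond at 10% | 0.8×25 + 0.2×10 = 22% | 0.8×10 + 0.2×10 = 10% | 12 | 3 |
| 20% in both arms, S-ketamine drop-outs all non-responders, control random | 20% | 10% | 10 | 5 |
| 30% vs 10%, all non-responders | 0.7×25 = 17.5% | 0.9×10 = 9% | 8.5 | 6.5 |

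**4. ML against MI.** A large-sample simulation used 200,000 and 100,000 patients, one earlier and one final score, and no true effect. Between-patient SD was 1.5 and residual SD 1.2, so the two scores correlate at 2.25 / (2.25 + 1.44) = 0.61. Drop-out was 20% per arm. It depended on the unseen final score on S-ketamine and was random on control. All these settings are assumptions.

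- True difference: −0.004
- ML: −0.379
- MAR-based MI: −0.379

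The two methods agree to within 0.001 and are equally wrong, although both used the earlier score.

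**5. False-positive rate.** This null simulation used 70:35 patients, 4,000 runs and Fisher's test at 0.0125. Only S-ketamine non-responders dropped out (20%), and control drop-out was random at 20%. An observed-case test stands in for MAR imputation without predictors. The expected spurious difference is p/0.8 − p.

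| True rate in both arms | Expected difference | Simulated | Rejections (nominal 1.25%) |
|---|---|---|---|
| 10% | 2.5 points | 2.6 | 0.5% |
| 30% | 7.5 points | 7.9 | 2.9% |
| 50% | 12.5 points | 12.6 | 6.2% |

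**The case against.** **The validity sentence is only a justification, and MAR-based MI is a conventional primary analysis.** This is true: correcting the sentence leaves the primary method unchanged. But the sentence is offered as a reason for the choice, and it removes the apparent need for any check. An analysis plan that is not shown cannot make it correct.

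**The illustration is extreme.** This stands. The 30% versus 10% split has no source, and at 2:1 it means (2×30 + 10)/3 = 23.3% missing overall, not 20%. The BPI is collected at all six visits (Table 1), so drop-out foreshadowed by earlier scores is partly MAR and MI can use it. With no true effect, drop-out at the same rate and of the same kind in both arms creates no spurious difference. At the planned 10% control rate the null simulation showed no inflation. Inflation needs a mechanism that differs between arms and response rates nearer the 28% and 56% that the Sample size estimation section reports for earlier treated patients.

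**Three stronger readings are tempting, and the article supports none of them.**

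- A reader might infer that the plan offers the ML-versus-MI comparison as a check on MNAR. It gives no purpose. One can say only that the comparison could not serve as such a check.
- A reader might infer that the whole planned test is impossible. Its MCAR part is feasible; only the MAR/MNAR step is not.
- A reader might infer that informative drop-out will go unexamined. The Missing data section plans to look into causes, and a full protocol or analysis plan may add sensitivity analyses. Their absence from a condensed article is not the finding.

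**Conclusion.** The point holds in a limited form. The article makes two affirmative errors. It ascribes to MI a validity under MNAR, and to ML and MI an unconditional unbiasedness, that they lack as specified. It also promises to classify missingness in a way that observed data do not allow. The ML-versus-MI comparison cannot make up for either.

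The error could run from nothing, if MAR holds given the earlier visits, to 3 points (12 rather than 15) with 20% missing in both arms, or 6.5 points (8.5 rather than 15) with 30% versus 10% missing. The last two are worst-case figures: they assume that every drop-out is a non-responder and that earlier visits are uninformative. They are not forecasts. The wording errors rest on no such assumption.

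**What to change.** 1. In Statistical analysis, delete the claim of validity under all three mechanisms. State that the primary MI and ML analyses assume MAR, and make the statements on unbiasedness and p values conditional on it.
2. State that the imputation model includes arm, baseline BPI and the BPI at all visits.
3. In Missing data, drop the promise to test MAR against MNAR. Keep the description of causes by arm and any check of MCAR.
4. Prespecify two MNAR sensitivity analyses of the BPI responder endpoints at the end of follow-up: (a) missing counts as non-responder; (b) delta-adjusted MI, worsening imputed BPI scores by arm before the 2-point and 1-point thresholds are applied, and reporting the delta at which the conclusion changes. The second is needed because the first is not conservative when control loses more patients.
5. If the ML-versus-MI comparison stays, say that it does not address MNAR.

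While this text is open, reconcile the missed-appointment rule with the intention-to-treat analysis in the Abstract, because it affects which partial records reach the imputation.

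The cost is a few sentences and a little more programming. The conclusion may look less certain. The changes are best made before any outcome data are seen.
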